## Methods

### Study Design

This is an intention-to-treat, single-blind, parallel, 2-arm clustered randomized controlled trial study. We will collect data at baseline (T1) and measure outcomes after program completion (T2) and follow-up at 3 months (T3) and 6 months (T4) to test our hypotheses. We include a retention period of 6 months to determine whether fall risk, dynamic balance, PA, altered maladaptive FRA (FRA shifting), and negative self-perceptions of aging are maintained without ongoing intervention. This study is registered on ClinicalTrials.gov (NCT05778604).

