### Recruitment, Randomization, and Procedures

Research sites will be recruited through a partnership with local communities, personal contacts, referrals, and phone calls. The unit of randomization is an independent living senior community, which is defined as a company-owned facility with a design for low-income independent adults aged ≥55 years and without health care services provided on campus. Research sites will be selected based on the prespecified criteria, including the number of residents, geographic proximity (urban vs suburban), and ability to implement the intervention. We plan to recruit 6 sites (3 intervention sites and 3 control sites). Collectively, approximately 10 sites and 800 low-income individuals are available for screening, and we can add sites, as they are abundant in the area. The participating sites will be randomized to either the intervention or control group in a 1:1 ratio. RX (coinvestigator and statistician) will use a computerized pseudorandom number generator to determine the randomization order in advance. The project director (PD) will reveal the randomization of the sites before the study [57]. Following randomization, we will recruit participants using standard strategies, including placing flyers on information boards and participating in open-house sessions or health fairs for face-to-face recruitment. Participants will also be recruited from their units by email. We will screen participants by a phone call to determine their initial eligibility, and those eligible will be invited for the baseline assessment. The research staff will explain the study and complete the consent process. The PEER intervention sites will be required to select 6 to 7 volunteers called *peer coaches* (PCs) to lead the exercise group, and the PCs will be eligible if they report having a regular PA routine or having an educational background in health care; are aged >55 years; can read, write, and understand English and Spanish; and are committed to delivering the protocol for 8 weeks. JS (coinvestigator) and the principal investigator (PI) will provide two, 3-hour sessions to train the PCs in balance and strength training, safety in the exercise, and participant motivation in collaboration with a successful PC from our pilot study. Each PC will be matched to 8 to 10 low-income older adults in the PEER group according to the place of residence and will supervise low-income older adults in groups while they are engaged in group exercises. This procedure was successful in our pilot study.

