### Data Analysis

We will collect demographic information from the participants for the study. We will compare baseline variables, such as essential participant characteristics, primary, and secondary end points, to summarize the differences between the 2 groups at the start of the study (T1). For the analysis of categorical data and continuous data, the chi-square test and 2-tailed *t* test will be used. We use R (version 4.1.2; R Foundation) for data analyses, with a significance level of *P*=.05.

Aim 1 is to examine the effects of the technology-based PEER intervention on fall risk, dynamic balance, and accelerometer-based PA.

The hypotheses are as follows:

*H 1.1*: The PEER group will reduce the fall risk compared with the control group.*H 1.2*: The PEER group will improve the dynamic balance compared with the control group.*H 1.3*: The PEER group will improve accelerometer-based PA compared with the control group.

Data will be analyzed according to the intention-to-treat principle [100]. We will model the fall risk, dynamic balance, and accelerometer-based PA as longitudinal outcomes consisting of 4 measurements (baseline or T1, after program completion or T2, follow-up at 3 months or T3, and follow-up at 6 months or T4) using the longitudinal linear mixed model (LMM) [101]. The LMM allows all low-income older adults and their available data to be included in the analysis, even for unequal group sample sizes, and the group heterogeneity can be addressed in the variance structure of random effects. It is hypothesized that the PEER group will show improvement in all outcome measures over time. To test hypothesis *1.1*, between-arm differences for fall risk scores, the likelihood ratio test (LRT) [101] associated with LMM will be used from all follow-up assessment visits. Similarly, the LRTs will be used to test hypotheses *1.2* and *1.3* for between-arm differences for dynamic balance and PA, respectively. The CDC-recommended scoring scheme will be adopted to process fall risk, TUG, and STS data [102]. For example, the average score of the number of STS repetitions a person can complete is based on different age and sex groups [102].

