*H 2.1*: The PEER group will have a more adaptive shifting compared with the control group.*H 2.2*: The PEER group will have a more positive shift in their perceptions of aging compared with the control group.

To test hypothesis *2.1* (FRA shifting), the 4 FRA quadrants will be determined by grid coordinates based on 2 continuous level measures (BBS and short FES-I scores). We will classify shifting into 2 types: maladaptive and adaptive shifting. Adaptive shifting is moving from irrational, incongruent, or congruent to rational. The outcome is a percentage of low-income older adults with baseline (T1) in irrational, incongruent, or congruent quadrants who end up in the rational quadrant after program completion (T2). Maladaptive shifting is a movement from rational to any other quadrant, and the percentage of low-income older adults will be calculated. After program completion (T2), the baseline FRA categories (T1) may remain the same or shift to a different FRA category. We will form a 4×4 contingency table for the 4 FRA categories at each follow-up time point (T3 and T4) to summarize the shifts. The standard 4×4 table analysis will be performed to examine the FRA shifting, either using a chi-square test or exact test, depending on the actual counts observed in the 4×4 table. The BBS and short FES-I scores will be collected in 4 planned visit time points (T1, T2, T3, and T3). We will use the Generalized Linear Mixed Model (GLMM) to analyze these 2 end points for assessing the difference between the PEER intervention and control arms on the shift of FRA categories [109]. Our longitudinal data on the PEER effects of different types of shifting on low-income older adults will contain repeated binary measures of the shifting status over time. The binomial GLMM with the logic link will allow us to assess the difference between the 2 arms in FRA shifting, and the associated LRT [101] will be used to test hypothesis *2.1* if a significant adaptive shifting is detected in the PEER group compared with the control group. The GLMM can address the group heterogeneity by specifying the corresponding covariance structure in random effect terms.

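### Sites are randomised (6 planned, 3 per arm), but no arm comparison names site, and the likelihood ratio test suits about 4 between-site degrees of freedom poorly unless site variation is negligible

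*Protocol article*

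**What the plan says.** Study Design: "This is an intention-to-treat, single-blind, parallel, 2-arm clustered randomized controlled trial study". Recruitment, Randomization, and Procedures: "The unit of randomization is an independent living senior community", "The participating sites will be randomized to either the intervention or control group in a 1:1 ratio", and "We plan to recruit 6 sites (3 intervention sites and 3 control sites".

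Data Analysis fits longitudinal linear mixed models to four visits for Aim 1. For fall risk, "the likelihood ratio test (LRT) [101] associated with LMM will be used from all follow-up assessment visits", and the same test serves dynamic balance and physical activity. On random effects it says only that "the group heterogeneity can be addressed in the variance structure of random effects". The adjustment factors it lists (age, sex, perceived health, earlier falls) are all participant-level. A group-by-time term is added to judge the effect during follow-up.

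For H2.1, "The binomial GLMM with the logic link will allow us to assess the difference between the 2 arms in FRA shifting", again with a likelihood ratio test, beside chi-square or exact tests on 4×4 tables. H2.2 uses a longitudinal mixed-model analysis of variance. On the level: "We use R (version 4.1.2; R Foundation) for data analyses, with a significance level of *P*=.05". Site, community or cluster appears nowhere in Data Analysis.

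**The concern.** All participants at a site share one arm, so the arm effect can be judged only against variation between sites. With three sites per arm that variation rests on 6 − 2 = 4 degrees of freedom. A model with participants but no sites takes its standard error from variation between people. A model with a site intercept, tested by a likelihood ratio against chi-square, treats a variance estimated from six sites as if it were well known.

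Site differences are plausible here. Exercise is led by peer coaches matched to participants by place of residence, and a research assistant is to be trained at each site to run the balance test. If such variation exists and is not modelled, it can appear as an intervention effect on the primary outcomes and on appraisal shifting. The article looks ahead to large-scale use, so a false positive would matter.

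**Working it through.** **Inputs from the article.** 6 sites, 3 per arm; 240 completers, so 240/6 = 40 per site; 340 enrolled, so 340/6 ≈ 57 per site; α = 0.05; 4 visits, 3 of them follow-up.

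**Assumed.** Site ICC ρ from 0 to 0.05; within-person correlation between visits 0.8; equal site sizes; normal outcomes; two-sided tests. The only ICC in Power Analysis and Sample Size is 0.8, with no level stated, so it is not used as a site ICC.

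**1. The plan's own figures.** The only error rate stated is the nominal 5%. The stated 120 per arm can be checked with n = 2(1.96 + 0.84)²/d². At d = 0.25 this gives 252 per arm. With a repeated-measures factor of (1 + 3×0.8)/4 = 0.85 it gives 214. Neither is 120. At d = 0.36, the value given for secondary outcomes, n = 122. So 120 matches an unclustered two-sample calculation and shows no sign of a design effect.

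**2. Arm contrast over follow-up, site ignored.** With one outcome per person, DE = 1 + (m − 1)ρ and true error = 2[1 − Φ(1.96/√DE)]. For m = 40 and ρ = 0.01: DE = 1.39, 1.96/√1.39 = 1.66, error 9.6%. Averaging three visits removes within-person noise and raises the effective ICC to 0.01/(0.8 + 0.2/3) = 0.0115, so the simulated error on three-visit means is slightly higher.

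| Site ICC | DE | Formula, site ignored | Simulated LRT, site ignored | Simulated LRT, site intercept | Simulated t on 4 df |
|---|---|---|---|---|---|
| 0 | 1.00 | 5.0% | 5.0% | 3.7% | 4.9% |
| 0.001 | 1.039 | 5.5% | 5.6% | 4.1% | 5.0% |
| 0.01 | 1.39 | 9.6% | 10.4% | 6.6% | 4.8% |
| 0.02 | 1.78 | 14.2% | 15.8% | 8.6% | 5.0% |
| 0.05 | 2.95 | 25.4% | 28.2% | 11.2% | 4.9% |

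The simulated columns use 100,000 runs with 40 per site. With a single outcome per person, the site-intercept LRT gives 6.3%, 8.2% and 10.8% at ICC 0.01, 0.02 and 0.05. With 57 per site and three-visit means, at the same ICCs, the LRT gives 12.8%, 19.9% and 34.4% if site is ignored, and 7.5%, 9.7% and 12.0% with a site intercept.

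**3. Why a site intercept alone is not enough.** In balanced data where site variation dominates, the maximum-likelihood LRT equals 6·ln(1 + t²/4), with t the site-level t statistic. Setting this to 3.84 gives t² = 4(e^0.64 − 1) ≈ 3.59, so |t| ≈ 1.89. On 4 df that has a two-sided tail of 13.1%; the correct cutoff is 2.78. So 13.1% is the limit that the site-intercept column approaches.

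**4. Group-by-time test.** Site effects that are constant over time cancel, and simulated error is 5%. At site ICC 0.01 with site effects that drift:

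| Site correlation over time | LRT, person intercept only, 57 per site | F test, person and site intercepts, 40 per site |
|---|---|---|
| 0.9 | 10.6% | 9% |
| 0.8 | 17% | 13% |
| 0.5 | 35% | 26–27% |

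Intercepts alone do not help, because both cancel from this contrast. In a balanced 240 × 4 layout the error df are (240 − 2)(4 − 1) = 714, not about 4.

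**5. Power of a valid test.** For a t test on six site means of three-visit averages, SE = √{(2/3)[ρ + (0.8 − ρ + 0.2/3)/40]}. At ρ = 0.01, SE = 0.145 and d/SE = 0.25/0.145 = 1.73, which on 4 df gives 27% power. At ρ = 0, 0.02 and 0.05, power is 36%, 22% and 15%.

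**The case against.** Much of the case on the other side stands.

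- A reader might infer that the plan is certain to give false positives well above 5%. The article does not support that. It gives no identifiable site ICC, and the error is nominal at ICC 0 and about 5–6% at 0.001. Reading the stated 0.8 as a site ICC would give an extreme answer, but its level is not stated.
- A reader might infer that any stable difference between communities would be declared an effect. In the group-by-time contrast such differences cancel. However, the article also speaks of between-arm differences over the follow-up visits, so that protection cannot be presumed.
- The chi-square reference for the likelihood ratio test is the usual default, but it is inferred and not stated.
- The remark on group heterogeneity might mean sites. It follows a mention of unequal group sizes, where group reads as arm, and it says only what can be done. If it does mean sites, step 3 still applies.
- H2.2 is not tested by likelihood ratio. The objection there is only that site is missing.
- Six sites is a plan, not a cap. About ten are said to be available and more can be added.
- Baseline significance tests are a matter of preference here and are no part of this point.

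It can also be said that random-effect structure and df methods belong in an analysis plan that is not shown. That would answer silence. The article is not silent: it fixes the model family, the test, the level, the covariates and the interaction, and followed as written these leave out the randomised unit.

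**Conclusion.** The analysis is wrong as written. Six whole sites are to be randomised, no arm comparison names site, and the likelihood ratio test named for H1.1–H1.3 and H2.1 is not suited to about 4 between-site df even if a site intercept is intended.

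The size depends on an unknown site ICC. For an arm contrast with site ignored, error is at least about twice nominal from a site ICC of roughly 0.01 and close to nominal at 0.001 or below. With a site intercept and chi-square reference the inflation is smaller, and at very small ICC the test is slightly conservative. The group-by-time test is sound if site effects are constant over time and inflated if they drift. The figures assume equal site sizes, normal outcomes and a within-person correlation of 0.8. They were not computed for the binary shifting outcome, where the same structural fault applies.

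**What to change.** - Name site in every arm comparison, including H2.2: a random intercept for site, participant within site, and a site-by-time random term wherever group-by-time is tested.
- Fit by REML and test arm and arm-by-time contrasts with Kenward-Roger or Satterthwaite df, in place of the likelihood ratio test. Alternatively, compare site means, or site mean changes, by a t test on (sites − 2) df.
- For binary shifting, use a two-stage site-level comparison or a small-sample-corrected GLMM. Keep the 4×4 chi-square or exact tests descriptive.
- Say which contrast decides each hypothesis: the arm difference over follow-up or group-by-time.
- A permutation test over sites is no way out at 3 v 3: there are 20 allocations, so the smallest two-sided p is 2/20 = 0.10.

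**Cost.** The analysis change is wording and standard R packages. The statistical cost is real: confidence intervals widen, and with six sites of 40 completers and d = 0.25, power is about 27% at site ICC 0.01 and 15% at 0.05. The stated 80% should therefore be restated for the clustered design with an explicit site ICC. The article leaves room to add sites, and ten sites would give 10 − 2 = 8 df.

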### Power Analysis and Sample Size

The sample size estimate was based on the primary outcomes of fall risk (CDC fall risk score) and PA (normalized MVPA) for aim 1 and the secondary outcome of FRA shifting (BBS score) for aim 2. The difference in the normalized mean MVPA between the PEER group (mean 3.67, SD 2.54) and the control group (mean 5.38, SD 2.68) and the difference in the fall risk score between the PEER group (mean 2.72, SD=3.23) and the control group (mean 2.21, SD=2.06) are considered markers of PA and fall risk, respectively. Considering a clinically relevant normalized difference in MVPA of 1.7 (SD 2.60) and a fall risk score difference of 0.50 (SD 2.56), the medium effect size Cohen *d*=0.25, intraclass correlation (ICC) of 0.8, and a significance level of are used for the calculation of the sample size. A sample size of 120 participants per arm is needed to reach 80% statistical power to detect the difference between the PEER and control groups on repeated measures of normalized MVPA. A sample size of 120 participants per arm is needed to reach 80% statistical power to detect the difference between the PEER and control groups on repeated measures of normalized MVPA.

In addition, the sample size was also based on the following: (1) at least 3 sites per arm; (2) an initial hypothesis that at least 10% (34/340) of the irrational, incongruent, and congruent FRA would shift to rational FRA after PEER completion; (3) an approximate study adherence rate of 80% [56], and (4) an estimated study dropout rate of approximately 40% (136/340) over time. Therefore, the sample size was increased from 120 to 170 per arm, resulting in a total of 340 participants. On the basis of our pilot study [26], we estimate that approximately 60% (204/340) of the low-income older adults will meet all inclusion and exclusion criteria and will be interested in participating in this study. We estimate that a minimum of 567 low-income older adults will be screened to identify 340 low-income older adults for enrollment, and approximately 240 low-income older adults (120 per arm) are needed to complete the study. Given the sample size of 120 per arm, a significance level of *P*=.05, and 80% power, considering a clinically relevant BBS mean score difference of 8 (SD 12), the effect size Cohen *d*=0.36 can be achieved to compare the intervention effect based on secondary outcomes.

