### End Points

The intervention will be delivered per protocol until 1 of the following end points is met (whichever occurs first): (1) unable to participate in PEER activities (eg, exercise), (2) past 8 weeks of enrollment, and (3) other exclusion criteria are met (eg, severe cognitive problems).

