### Control Group

The control group or enhanced usual care will receive an information pamphlet about falls (English or Spanish version) developed by the CDC Stopping Elderly Accidents, Deaths, and Injuries–Older Adult Fall Prevention. These pamphlets provide details on fall risk, ways to prevent falls, how to check for safety, postural hypotension, chair rise exercise, what they can do to avoid falls, ensure safety, and manage postural hypotension [2]. The control group will be encouraged to discuss fall prevention with their primary care provider and continue their regular activities for 6 months. They will be offered the PEER intervention when the study concludes. They will receive monthly phone calls from the RA to record a monthly fall incidence log.

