Raw acceleration data from ActiGraph will be downloaded and converted to “.csv” files using ActiLife 6 Software (version 6.13.4; ActiGraph LLC). PA data will be processed using the R package *GGIR* (version 2.4-0). *GGIR* R package used to process multiday raw accelerometer data for PA research [103] includes (1) auto-calibration of acceleration signals according to local gravity [104], (2) detection of nonwear time, and (3) calculation of the average magnitude of dynamic acceleration corrected for gravity (ie, Euclidean Norm Minus One) over 5-second epochs and expressed in milli-gravitational units (mg) [105]. Nonwear time and sustained abnormally high accelerations will be imputed using the default settings [105]. The Euclidean Norm Minus One cut-off points will be used to estimate the total time spent in sedentary behavior, light intensity PA, and MVPA in participants.

For missing data treatment, the missing values will be imputed using the method of multiple imputations [106]. The maximum number of missing values within a scale will be based on the guidelines provided by the scale developers or based on a limit of 25% missing values. In the first analysis, all low-income older adults will be included according to their original group assignment [100]. Participants in the PEER group who completed at least 5 of the 8 group-based sessions will be included in the per-protocol analysis. Although every attempt will be made to ensure that low-income older adults complete all assessments, there may be some participant attrition over time. The missing data mechanism is assumed to be missing at random. The dropout patterns or missing data rates for the 2 arms will be examined to assess the differences. When possible, the models should be modified to account for relevant factors such as age, sex, general health perception, and the number of falls in the 6 months leading up to the baseline. To determine the impact of the PEER intervention during follow-up evaluations, the group-by-time interaction term will be incorporated into the model. Effect sizes (Cohen *d*) [107,108] will be calculated based on the estimated means and the pooled SD.

Aim 2 is to examine the effects of the intervention on FRA shifting and negative self-perceptions of aging.

The hypotheses are as follows:

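### The per-protocol set is filtered on attendance in the PEER arm only, so it is not a randomised comparison and is likely, though not certain, to favour PEER

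*Protocol article*

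**What the plan says.** The trial randomises sites to PEER or enhanced usual care. For Aim 1, Data Analysis states: "Data will be analyzed according to the intention-to-treat principle". On analysis sets it says: "In the first analysis, all low-income older adults will be included according to their original group assignment". The next sentence defines the second set: "Participants in the PEER group who completed at least 5 of the 8 group-based sessions will be included in the per-protocol analysis". It gives no inclusion rule for controls and does not say which controls are compared with these attenders.

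Under Control Group, controls get a pamphlet, and "The control group will be encouraged to discuss fall prevention with their primary care provider and continue their regular activities for 6 months". They are offered PEER only when the study concludes. Their one regular contact is by telephone: "They will receive monthly phone calls from the RA to record a monthly fall incidence log". They have no group sessions.

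Under End Points, one condition that ends delivery for a PEER participant is being "unable to participate in PEER activities (eg, exercise"). Another is meeting exclusion criteria such as severe cognitive problems.

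The only attendance-like planning figure, under Power Analysis and Sample Size, is "an approximate study adherence rate of 80"%. It is not defined as 5 of 8 sessions.

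**The concern.** Randomisation makes the two arms comparable as allocated. Keeping only PEER participants who reach 5 sessions removes low attenders from one arm, while the controls who would have attended poorly cannot be identified. Attendance is plausibly linked to the outcomes (fall risk, balance and activity), and the article supplies one link itself: someone who becomes unable to exercise stops receiving PEER, may fall short of 5 sessions and leaves the set. A control with the same decline meets no stated exclusion.

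The per-protocol figure could then be taken as the effect of actually receiving PEER when part of it is selection. A control rule based on completed calls or assessments would not cure this, because it would not pick out the same kind of people as attending exercise sessions does.

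**Working it through.** The article gives no sample size, effect or error rate for the per-protocol analysis, so there is no figure to reproduce. What follows is an illustration with no true PEER effect and outcomes scored so that higher is better.

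**Inputs**
- Rule: at least 5 of 8 sessions, PEER only (Data Analysis).
- Share of PEER retained, p: 0.80, borrowed from the adherence figure, and 0.60. Both are assumptions.
- Correlation r between propensity to attend and the characteristic that drives it: 0.2 to 0.4, an assumption.
- Planned model: a mixed model on four visits including baseline, with a group-by-time term. Covariates are added only when possible (Data Analysis).
- Yardsticks from Power Analysis and Sample Size: fall risk 0.50/2.56 = 0.20; stated d = 0.25; normalised MVPA 1.7/2.60 = 0.65.

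**Step 1. Follow-up scores with no adjustment.** Keeping the top share p of one arm shifts its mean by r × φ(z)/p, where z is the cut-point and φ the normal density.
- p = 0.80: φ(z)/p = 0.350, so the shift is 0.2 × 0.350 = 0.070 to 0.4 × 0.350 = 0.140 SD.
- p = 0.60: φ(z)/p = 0.644, so the shift is 0.2 × 0.644 = 0.129 to 0.4 × 0.644 = 0.258 SD.

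This is not the planned analysis, which uses the baseline visit.

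**Step 2. Estimators closer to the plan.** The simulation had 400,000 people per arm and no effect. The baseline score had SD 1, with stable variance 0.8 and occasion variance 0.2. Individual change had SD 0.5. All of these are assumptions. The change score stands in for the group-by-time term. Ranges cover r = 0.2 and 0.4 and p = 0.8 and 0.6; positive values favour PEER.

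| What drives attendance | Change score | Baseline-adjusted | Follow-up score alone |
|---|---|---|---|
| Stable trait | −0.004 to 0.001 | 0.012 to 0.046 | 0.058 to 0.229 |
| Observed baseline score | −0.052 to −0.014 | 0.000 to 0.002 | 0.056 to 0.209 |
| The person's own change during the programme | 0.035 to 0.127 | 0.034 to 0.129 | 0.032 to 0.134 |

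Simulation error is at most about √(1.25/240,000 + 1.25/400,000) = 0.003, so values within a few thousandths of zero are zero.

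**Step 3. Check of the last row.** The shift should equal 0.5 × r × φ(z)/p. The smallest is 0.5 × 0.2 × 0.350 = 0.035 and the largest 0.5 × 0.4 × 0.644 = 0.129, which agrees. The bias is proportional to the assumed SD of change, so halving that SD halves the bias.

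**Step 4. Against the planning effects.** A bias of 0.03 to 0.13 SD is 15% to 65% of 0.20, 12% to 52% of 0.25, and 5% to 20% of 0.65.

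**The case against.** The strongest reply has four parts.

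- **The comparator is inferred.** The article does not say that every control is kept. A control-side rule may stand in the full protocol or analysis plan, which are not shown. This is right, so the point should not be read as saying that all controls stay in. The rule as stated still selects one randomised arm on behaviour after randomisation.
- **Nothing confirmatory rests on it.** Intention to treat comes first, and no hypothesis or power statement is tied to the per-protocol set. This stands and limits the weight of the point.
- **The larger figures belong to another analysis.** A reader might infer from Step 1 that selection alone could supply about a third to all of the target effect. The documents do not support that. It needs unadjusted follow-up scores, an attendance of 60% that has no source, and only the smaller planning effects as yardstick. One reservation remains: Cohen d is to be computed from estimated means. If those are follow-up levels alone, stable traits would not cancel.
- **The complier-average estimate has its own weakness.** PEER also delivers physio-feedback, cognitive reframing and home exercise. The planned home exercise is at least 2 × 30 = 60 of the 120 minutes a week. People with fewer than 5 group sessions may benefit from these, so the estimate could be too large. Using number of sessions as the exposure does not settle this, because it needs the same assumption at zero sessions. Participants are also recruited after sites are randomised, so any recruitment imbalance would be magnified. All of this stands, and the estimate can only be supportive.

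**Conclusion.** The point holds in a limited form. The per-protocol set is restricted on attendance after randomisation in PEER alone, so its comparison has lost the protection of randomisation. Bias towards PEER is likely but not certain, and its size and sign depend on why sessions are missed. With the planned type of model it is about 0.03 to 0.13 SD towards PEER if people who deteriorate stop attending. It is near zero if attendance follows stable traits (up to about 0.05 SD with baseline adjustment), and 0.01 to 0.05 SD against PEER on a change score if attendance follows the baseline score. These figures rest on the assumed correlations, retention shares and SD of change, none of which the article gives.

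A reader might go further and infer that the trial's main conclusions are compromised. They are not, because the intention-to-treat analysis does not use the attendance rule.

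**What to change.** 1. State which controls form the per-protocol comparator and any criterion they must meet.
2. Label the attendance-filtered comparison as descriptive, not as evidence of efficacy.
3. Estimate the effect of attendance with a complier-average analysis that uses randomised arm as the instrument for at least 5 of 8 sessions, with site-level error and baseline covariates. As controls cannot attend during follow-up, this amounts to the intention-to-treat estimate divided by the share of PEER reaching 5 sessions. The multiplier would be 1/0.8 = 1.25 at 80% and 1/0.6 = 1.67 at 60%.
4. State its assumption of no effect of assignment below 5 sessions. Say that physio-feedback, reframing and home exercise may violate it and make the estimate too large. Report it as a sensitivity analysis beside the intention-to-treat result.

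The cost is a few sentences in the plan and a short analysis on attendance data that the existing rule already requires. The downside is wider intervals (the multipliers above apply to them too, before uncertainty in the share) and an assumption that can be only partly tested.

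### The named test of H2.1 (FRA shifting) is not tied to its T2 outcome, and the stated 80% power belongs to a BBS mean, not to shifting

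*Protocol article*

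**What the plan says.** **Outcome.** Data Analysis (Aim 2) gives the adaptive-shifting outcome as a percentage: of those in the irrational, incongruent or congruent quadrant at T1, the share "who end up in the rational quadrant after program completion (T2"). Under FRA Shifting, the rational quadrant requires both BBS ≤30 and short FES-I ≤10.

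**Tables.** "We will form a 4×4 contingency table for the 4 FRA categories at each follow-up time point (T3 and T4) to summarize the shifts". A chi-square or exact test is to be run on the 4×4 table.

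**Models.** After introducing the BBS and short FES-I scores, the section proposes a generalized linear mixed model "to analyze these 2 end points for assessing the difference between the PEER intervention and control arms on the shift of FRA categories". It then says that the data on different types of shifting "will contain repeated binary measures of the shifting status over time", and names the likelihood ratio test (LRT) from a binomial mixed model as the test of H2.1. No visit, average or interaction term is attached to that test.

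**Power.** Power Analysis and Sample Size names "the secondary outcome of FRA shifting (BBS score) for aim 2" as one basis of the calculation. "Given the sample size of 120 per arm, a significance level of *P*=.05, and 80% power", it takes a BBS mean difference of 8 (SD 12) and reports Cohen d=0.36.

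**The concern.** Two things do not fit together.

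First, the outcome sits at T2, the tables at T3 and T4, and the model runs over all visits. The Study Design section asks separately whether effects last without ongoing intervention, so fading after T2 is a possibility that the trial itself anticipates. In that case the stated outcome and the named test can give different answers, and the text does not say which one settles H2.1. The response is open too. Adaptive shifting can occur only in people not rational at T1 and maladaptive shifting only in people who are rational at T1, yet the model is described for different types of shifting with no stated population.

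Second, a change in mean BBS is not a change of quadrant. BBS can improve without anyone crossing 30, and a participant in the irrational quadrant can become rational on short FES-I alone. A reader who takes the 80% as the power for H2.1 is misled.

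**Working it through.** **1. Time points side by side**

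| Item | Visit(s) | Compares arms? |
|---|---|---|
| Stated outcome (percentage shifting) | T1 to T2 | yes, by hypothesis |
| 4×4 tables, chi-square or exact test | T3, T4 | not by itself |
| Binomial mixed model with LRT (named for H2.1) | shifting status over time | yes, contrast not stated |
| Mixed model of BBS and short FES-I | T1 to T4 | yes |

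T2 data do enter the LRT, but no listed analysis isolates T2. H1.1 and H2.2 are each said to use all follow-up visits; H2.1 carries no such statement. As an illustration, if the effect is δ at T2 and nil at T3 and T4, an equal-weight average over the three visits is (δ+0+0)/3 = δ/3.

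**2. The plan's own power figure**

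Inputs from Power Analysis and Sample Size: 120 per arm, alpha .05, 80% power. Two-sided testing is assumed; the article states it only for the *t* test.

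- Detectable d = (1.960 + 0.842) × √(2/120) = 0.362 (t-based 0.363). The stated 0.36 reproduces as a minimum detectable effect for a continuous measure.
- From the stated BBS inputs, d = 8/12 = 0.67. That needs 36 per arm for 80% power, and at 120 per arm the power is 99.9%.
- To reconcile 0.36 with SD 12, the difference would be 0.36 × 12 = 4.3. With a difference of 8, the SD would be 8/0.36 = 22.2.

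**3. Power for the stated H2.1 outcome**

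Inputs:
- PEER shift rate 10%: the plan's hypothesis in the sample-size section.
- Control rate: none is given there. The Discussion reports none of 22 pilot controls shifting. The 2% and 5% rates below are assumptions.
- Denominator: only people not rational at T1 can shift adaptively. As a rough proxy, the Introduction puts maladaptive FRA at 64% to 79%: 120 × 0.64 ≈ 77 and 120 × 0.79 ≈ 95 per arm.

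Formula: power = Φ[(|p1−p2| − 1.960 × se0)/se1], with se0 = √(2p̄(1−p̄)/n), p̄ = (p1+p2)/2 and se1 = √((p1(1−p1)+p2(1−p2))/n).

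Example with n=77, p1=0.10, p2=0.02: se0 = 0.0383, se1 = 0.0377, so Φ[(0.08 − 0.0750)/0.0377] ≈ 0.55.

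| Control rate | n=77 per arm | n=95 per arm |
|---|---|---|
| about 0% (pilot) | 82% | 89% |
| 2% (assumed) | 55% | 64% |
| 5% (assumed) | 22% | 26% |

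If all 120 per arm were at risk, the figures would be 95%, 75% (74.5% before rounding) and 31%. None allows for clustering by site, which would lower them.

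**The case against.** **A test is named.** The article assigns the LRT from the binomial mixed model to H2.1 and uses that phrasing for no other analysis. This stands: what is open is the contrast, visit and response inside the LRT, not which test is used.

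**A reader might infer several full-alpha routes to H2.1.** Data Analysis sets a single level ("We use R (version 4.1.2; R Foundation) for data analyses, with a significance level of *P*=.05"), and the tables, the score models and the LRT all bear on shifting. One could then compute an inflated false-positive rate. The documents do not support that. The tables are introduced as a summary, and a table of baseline by follow-up category does not compare arms. The sentence on the two scores can be read as leading into the binomial model. Nowhere is it said that any one positive result would be enough.

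**The pilot supports a control rate near zero**, where power is adequate. This stands as far as it goes, but it rests on 22 people, and the pilot percentages are reported for whole groups rather than for those not rational at T1.

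**d=0.36 may be meant only as the detectable effect**, with 0.67 comfortably above it. That would explain the number, but the sentence does not say so, and the measure would still be a BBS mean.

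**H2.1 is secondary and the article is condensed.** Contrast coding and labels for supportive analyses often sit in an analysis plan. That limits the weight of the point. It does not remove a conflict between statements in the article itself.

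**Conclusion.** The point holds in two parts. The H2.1 outcome is fixed at T2, while the listed analyses are at T3 and T4 or over time with no stated contrast, so the named test need not answer the stated outcome. And the 80% power is for a BBS mean difference, which is not the H2.1 outcome; its d=0.36 also disagrees with the 8/12=0.67 implied by the inputs beside it.

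How far true power falls short depends on a control rate that the sample-size section does not give: from 82%–89% at the pilot's 0% to 22%–26% at an assumed 5%. This rests on 10% shifting in PEER, 77 to 95 per arm at risk, two-sided .05 and no clustering. It would be wrong to infer that H2.1 is certainly underpowered, since at the pilot rate it is not. The defect is that the stated power does not speak to H2.1. As this is a secondary hypothesis and the repair is cheap, it should be corrected before outcomes are analysed.

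**What to change.** **Data Analysis, H2.1.** State that the LRT from the binomial mixed model tests the difference between arms in adaptive shifting at T2 among participants not rational at T1, which matches the outcome already defined. Label T3 and T4 as maintenance, add a T2 table, call the tables descriptive, and call the BBS and short FES-I models supportive. If a test over all follow-up visits is intended, as for H1.1 and H2.2, change the outcome definition to match; either choice is coherent.

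**Power Analysis and Sample Size.** Call the powered measure the BBS score and drop the equation with FRA shifting. Say that the 80% power applies to a BBS mean difference and not to adaptive shifting. Reconcile d=0.36 with 8/12=0.67. Restate power for the shift percentage with an explicit control rate, the expected number at risk and an allowance for clustering.

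**Cost.** Wording and one recalculation; no new data or participants. The power statement becomes less favourable, and under the T2 choice the T3 and T4 results are no longer confirmatory for H2.1.
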